### Experimental Intervention

Each participant will be randomized to receive active or sham treatment throughout the protocol, with 50% (28/56) receiving active treatment and 50% (28/56) of participants receiving placebo. We will use a T1 MRI to localize the FP stimulation site. This region is correlated with electrode FP2 on a 10 to 20 electroencephalogram, a region overlapping with the right VMPFC [22,82]. To ensure precise and repeatable coil positioning over the frontal pole FP2 site, the Localite (neuronavigation) system and an MRI instrument marker will be used at every iTBS session.

Our 9-minute iTBS protocol will be delivered using the MagVenture Mag-Pro X100 with the MagOption stimulator, including active and placebo coils (C-B60 Butterfly coils). The consensus in the literature is that iTBS can safely deliver 1800 pulses at 110% of the MT to the frontal pole [82,83]. iTBS parameters include 3 pulses of stimulation at 50 Hz, repeated every 200 miliseconds. The interpulse interval is 20 miliseconds. A 2-second train of TBS is repeated every 10 seconds for a total of 570 seconds, equaling a total of 1800 pulses delivered over 9 minutes. To ensure that the participants can tolerate the treatment, stimulation intensity will begin at 60% to 70% of the MT intensity and will slowly increase as the patient tolerates to 110% of the patient’s MT intensity over the first few treatment sessions [42].

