### Data Collection and Measures

#### MRI Data Acquisition, Neuronavigation, and Motor Thresholding

All participants will undergo an MRI of their brain before and after iTBS administration. Before iTBS, a high-resolution, 3D, T1-weighted, multigradient-echo sagittal anatomical scan (voxel size=0.8 mm isotropic resolution) will be collected at the University of Illinois, Chicago Center for Magnetic Resonance Research to allow for iTBS treatment site neuronavigation for each participant. Participants will also complete a resting-state functional MRI (fMRI) and diffusion tensor imaging before and after iTBS administration to examine treatment-induced connectivity changes. Participants will be asked to complete a standardized MRI safety screening form before starting the study to ensure the MRI safety procedures are followed (Multimedia Appendix 2).

Each participant’s T1 MRI will be loaded into a TMS Neural Navigator TS system (version 3.3.22, Localite), consisting of a camera and computer system that allows a TMS provider to superimpose an individual’s MRI onto where they are in space, allowing for very precise placement of the TMS coil. Electrodes will be placed on the thumb over the abductor pollicis brevis (ABP) muscle and connected to an electromyograph (MagVenture) to measure motor-evoked potentials (MEPs). To determine each participant’s motor threshold (MT) for iTBS (to determine at which intensity the iTBS stimulation should be delivered), a MagProX100 with MagOption stimulator and Magpro Cool Coil B65 A/P (MagVenture) will be used. Single pulse TMS will be administered to the left motor cortex at the hand knob. The location of this part of the motor cortex will be estimated using the participant’s MRI and then confirmed using TMS to identify the ABP muscle neural coordinates. The resting MT is the lowest stimulus intensity necessary to produce MEPs of the peak-to-peak amplitude of ≥50 µV in 5 of 10 trials. MEPs of the ABP will be recorded using surface electrodes on the right thumb. The right frontal pole will be identified and mapped using the TMS Neural Navigator (Localite) system. The anatomical location is easily identifiable using anatomical landmarks and correlates with electrode frontal polar cortex (FP; FP2) on a 10 to 20 electroencephalogram, a region overlapping with the right VMPFC [22,63,82]. Refer to Multimedia Appendix 3 for the equipment list.

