**Figure 2 figure2:**
[figure not shown]
Study visit diagram. iTBS: intermittent theta burst stimulation; MRI: magnetic resonance imaging.

After meeting with the research staff and signing the informed consent, participants will complete several baseline diagnostic and screening measures (Table 1). These measures will be used to track changes in symptoms of impulsivity, suicidality, depression, anger, aggression, and social and occupational functioning throughout the study. If the participant is a woman, sexually active, and not on any form of physician-prescribed birth control, they will be asked to take a urine pregnancy test at this visit. Veterans who have completed baseline measures and have met eligibility criteria will be asked to complete a pretreatment resting-state fMRI at the University of Illinois, Chicago, an institution partnering with us for this study (visit 2). After the pretreatment MRI, participants will be invited back to the Hines VA to complete their MT and brain mapping using the TMS Neural Navigator (Localite) system (visit 3).

Participants will be randomized to either active or sham treatment. Blinding procedures for active and sham iTBS will be delivered with the MagProX100 with MagOption stimulator and Magpro Cool Coil B65 A/P (MagVenture), which can be switched to active or sham. The coil is identical visually for the sham and active conditions. Veterans and researchers will wear headphones connected to the noise generator during treatment to hear active iTBS for both conditions, thereby maintaining the blind. The sham coil and scalp electrodes will be placed in the same location for all participants and will mimic the sensation produced by the active coil but will not alter brain physiology. Thus, the sham stimulation looks, sounds, and feels like active stimulation. A single unblinded study team member will determine which participants are randomly placed in the active or sham groups.

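### The stated train timing does not give 1800 pulses in 570 seconds or 9 minutes, and two sections name different treatment coils

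*Protocol article*

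**What the plan says.** **Timing.** The Experimental Intervention section gives the burst structure: "iTBS parameters include 3 pulses of stimulation at 50 Hz, repeated every 200 miliseconds", and "The interpulse interval is 20 miliseconds". It continues: "A 2-second train of TBS is repeated every 10 seconds for a total of 570 seconds, equaling a total of 1800 pulses delivered". The same sentence ends by putting the duration at 9 minutes, and the paragraph opens: "Our 9-minute iTBS protocol will be delivered using the MagVenture Mag-Pro X100". The figure of 1800 pulses appears twice in this section. The section TMS in Neuropsychiatry gives it again, as the daily count of the published protocol it cites, and describes the same rhythm of 50 Hz triplets at 5 Hz.

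**Coil.** Experimental Intervention describes the treatment equipment as "including active and placebo coils (C-B60 Butterfly coils"). Study Procedures, in the blinding paragraph after Figure 2, says that active and sham treatment are both delivered with the "Magpro Cool Coil B65 A/P (MagVenture), which can be switched to active or sham", and that this coil looks the same in both conditions. For the motor threshold, the section on MRI data acquisition, neuronavigation and motor thresholding says that "a MagProX100 with MagOption stimulator and Magpro Cool Coil B65 A/P (MagVenture) will be used". Experimental Intervention then sets treatment intensity as a percentage of that threshold, rising to 110%.

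**The concern.** Two separate specifications conflict.

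The first is the stimulation schedule. Burst structure, train length, train interval, total seconds, minutes and pulse count are all stated, so any one can be checked against the others. If they disagree, someone programming the stimulator or replicating the trial must choose which figure to ignore. The protocol treats pulse number as material: TMS in Neuropsychiatry describes the chosen number as lying in an optimal range and says that more pulses may be inhibitory.

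The second is the coil. Intensity is a percentage of a motor threshold, so the specification depends on which coil measured the threshold and which delivers treatment. The sham control depends on the coil as well, because the statement about a switchable, visually identical device is made for one named model only.

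**Working it through.** **Inputs, all from Experimental Intervention:** 3 pulses per burst; one burst every 200 ms; trains of 2 s; one train every 10 s; 570 s in total; 1800 pulses; 9 minutes.

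**Step 1. Internal check of the burst.** Pulses at 50 Hz are 1/50 s = 20 ms apart, which matches the stated interpulse interval. One burst every 200 ms is 5 Hz, which matches TMS in Neuropsychiatry. The burst description is consistent.

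**Step 2. Pulses per train.** (2 s / 0.2 s) × 3 = 10 × 3 = 30.

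**Step 3. Attempt to reproduce 1800.**

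| Reading | Trains | Pulses | Against 1800 |
|---|---|---|---|
| 570 s, 10 s from onset to onset | 570/10 = 57 | 57 × 30 = 1710 | −5.0% |
| Same, also counting a train that starts at second 570 | 58 | 58 × 30 = 1740 | −3.3% |
| 9 minutes taken literally (540 s), 10 s cycle | 54 | 54 × 30 = 1620 | −10.0% |
| 570 s, 10 s read as a gap after each train (12 s cycle) | 48 | 48 × 30 = 1440 | −20.0% |
| 540 s, 12 s cycle | 45 | 45 × 30 = 1350 | −25.0% |
| 570 s, 11 bursts per train | 57 | 57 × 33 = 1881 | +4.5% |
| 540 s, 11 bursts per train | 54 | 54 × 33 = 1782 | −1.0% |

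No reading gives 1800. The closest, 1782, needs a burst that starts at 2.0 s, outside the stated 2-second train, and it discards the stated 570 s. A pulse count is deterministic, so there is no rounding tolerance to appeal to.

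**Step 4. What 1800 would imply.** 1800 / 30 = 60 trains. At a 10 s cycle the last train ends at 59 × 10 + 2 = 592 s (600 s in full cycles), which is 22 to 30 s more than stated. To fit 60 trains into 570 s, the cycle would be 570/60 = 9.5 s, or (570 − 2)/59 = 9.63 s if measured to the end of the last train. For 540 s the same sums give 9.0 and 9.12 s. These figures measure the mismatch and are not proposed settings.

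**Step 5. Seconds against minutes.** 570 / 60 = 9.5 minutes, not 9.

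**Step 6. Coil, section against section.**

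| Purpose | Section | Coil named |
|---|---|---|
| Motor threshold | MRI data acquisition, neuronavigation and motor thresholding | Cool Coil B65 A/P |
| Treatment | Experimental Intervention | C-B60 Butterfly, active and placebo |
| Treatment and blinding | Study Procedures | Cool Coil B65 A/P, switchable |

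Two sections name the device for the same procedure and give different models. If Experimental Intervention is followed, the 110% is scaled to a threshold measured on another coil, and the article gives no way to relate the two.

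**The case against.** The strongest reply is that 1800 pulses is the consistent target and that only the description of the timing is loose. On that view nine minutes is a rough rendering of 9.5, the remaining gap is 22 to 30 seconds, and participants may well receive 1800 pulses. Much of this stands. A reader might infer from the table that participants receive 5 or 10% too few pulses, but the documents do not support that: they do not show which figure is wrong, and the 10% needs a literal 540 s, which is not written anywhere. The timing is also described once for both arms, so it creates no difference between them and does not touch the sample size or the primary analysis. What the reply does not remove is that the settings are said to equal 1800 and do not.

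On the coil, the plural in Experimental Intervention does not prove separate hardware, since Study Procedures also speaks of a sham coil and an active coil while describing one switchable device. The firm conflict is the model name. The equipment list in Multimedia Appendix 3 is not shown and may identify the coil, but it would not make the two sections agree.

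A reader might also infer that the blind is broken, or that the rater-administered primary outcome is compromised. Neither follows. The headphone noise and scalp electrodes in Study Procedures are not contradicted elsewhere, and nothing says that the raters operate or see the coil.

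**Conclusion.** Both contradictions stand as errors in the text.

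- **Timing:** the schedule as written gives 1710 pulses (1740 at most on the 10-second cycle over 570 s), against the stated 1800. The inconsistency is about 3 to 5% of pulses, and 10% only if 9 minutes is exact. The stated seconds and minutes also disagree. This rests only on the section's own figures, with the 10 seconds read from one train onset to the next. Reading it as a gap widens the difference.
- **Coil:** two sections name different models for treatment, and the motor threshold is tied to one of them. The effect on intensity is conditional: it arises only if the C-B60 is the coil actually used. In that case the statement about one switchable, visually identical coil would not describe the equipment either.

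These are operative specifications of the intervention in a sham-controlled device trial, and they cannot all be followed as written. They need correcting. They do not show that anyone was under-dosed or unblinded.

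**What to change.** 1. In Experimental Intervention, reconcile the pulse count, train interval, total seconds and session minutes so that they multiply out.
2. Reconcile the coil named for thresholding, for treatment and for blinding across the three sections, and make the blinding paragraph in Study Procedures describe the hardware in use.
3. Check the stimulator settings and the coil for any participant who has been treated. The Results section reports 2 participants enrolled as of July 2024 and does not say whether either had started treatment.

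Which values and which coil are right is for the investigator to state. The cost is a few lines of protocol wording and, if anyone has been treated, a look at the device settings. The sample size, the assessments and the analysis do not change.

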### Study Procedures

A partial HIPAA waiver and waiver of informed consent for screening purposes will provide regulatory approval to screen potential candidates to determine study eligibility. Once identified as a potential research candidate, candidates will be contacted for an initial phone screening to determine eligibility criteria. Demographics, mental illness diagnosis, current medication use, and history of impulsive behaviors (eg, history of fights, violence, anger, and irritability) will be cross-verified in the patient’s electronic medical record. A thorough chart review will be completed to cross-reference current medications with study eligibility criteria to identify antiepileptics or medications that could lower the seizure threshold. If review findings indicate possible contraindications to TMS or MRI related to a metal implant, then the model and manufacturer of the implant will be obtained to determine whether it is safe to expose the implant to a strong magnet. Manufacturer recommendations regarding safety will be followed. If potential participants meet all eligibility criteria, they will be invited for their first research visit, an in-person screening (visit 1). There will be 14 visits for this research study (Figure 2).

**Figure 2 figure2:**
[figure not shown]
Study visit diagram. iTBS: intermittent theta burst stimulation; MRI: magnetic resonance imaging.

After meeting with the research staff and signing the informed consent, participants will complete several baseline diagnostic and screening measures (Table 1). These measures will be used to track changes in symptoms of impulsivity, suicidality, depression, anger, aggression, and social and occupational functioning throughout the study. If the participant is a woman, sexually active, and not on any form of physician-prescribed birth control, they will be asked to take a urine pregnancy test at this visit. Veterans who have completed baseline measures and have met eligibility criteria will be asked to complete a pretreatment resting-state fMRI at the University of Illinois, Chicago, an institution partnering with us for this study (visit 2). After the pretreatment MRI, participants will be invited back to the Hines VA to complete their MT and brain mapping using the TMS Neural Navigator (Localite) system (visit 3).

Participants will be randomized to either active or sham treatment. Blinding procedures for active and sham iTBS will be delivered with the MagProX100 with MagOption stimulator and Magpro Cool Coil B65 A/P (MagVenture), which can be switched to active or sham. The coil is identical visually for the sham and active conditions. Veterans and researchers will wear headphones connected to the noise generator during treatment to hear active iTBS for both conditions, thereby maintaining the blind. The sham coil and scalp electrodes will be placed in the same location for all participants and will mimic the sensation produced by the active coil but will not alter brain physiology. Thus, the sham stimulation looks, sounds, and feels like active stimulation. A single unblinded study team member will determine which participants are randomly placed in the active or sham groups.

After the MRI and MT have been completed, participants will be randomized, and the intervention will begin (visits 4-13). Intervention sessions will occur once daily for 10 business days, with each session lasting 30 minutes to 1 hour. Research staff will complete a TMS safety rating scale before and after every iTBS session to assess for changes from baseline for vital signs, sleep duration, fatigue level, recent seizures, and tinnitus. Pain and tolerability measures will be completed at the end of every session to assess daily pain and session tolerability. After iTBS session 5 (visit 8), each participant will be asked to complete the self-report rating scales and neurocognitive testing they completed at baseline.

All veterans who have completed the iTBS treatment course of 10 sessions will be asked to return to the University of Illinois, Chicago’s Center for Magnetic Resonance Research to obtain a second resting-state fMRI for their final research visit. Posttreatment MRI data collection is expected to be completed 72 hours after the iTBS course. This time spacing between stimulation and imaging has been done in similar studies [78] and is thought to be a long enough gap post-iTBS completion not to represent the immediate effects of the most recent stimulation.

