### Participants

We will enroll 56 veterans aged between 22 and 65 years with a history of mTBI and impulsivity. They must also report that they have experienced SI within the last 3 months. mTBI will be defined according to the VA and Department of Defense guidelines [87] and use aspects of the mTBI symptom attribution and classification algorithm [88] when determining eligibility. mTBI must have occurred at least 1 year before enrollment to ensure that the injury has stabilized. Though it is not mandatory, veterans may also have diagnoses of depression, PTSD, or bipolar spectrum illness (without a history of psychosis). Recent SI (within the past 3 months) will be defined as a score of ≥1 on the Columbia Suicide Severity Rating Scale [89]. Impulsivity will be defined as having any mentions of impulsive behavior in the medical chart and any positive results on the Urgency, Premeditation (lack of), Perseveration (lack of), Sensation Seeking, Positive Urgency Impulsive Behavior Scale–Negative Urgency subscale (UPPS-P) [41]. For safety, we will exclude persons with contraindications to TMS or MRI because of increased risk of AEs. We will also exclude participants whose SI is active, with intent and plan, as they require emergency psychiatric intervention. We will not exclude individuals based on sex, gender identity, ethnicity, or race. To enhance generalizability, we will include veterans regardless of previous combat or deployment experience. As cannabis and alcohol use is prevalent among veterans, intermittent or low amounts of cannabis or alcohol consumption will not be considered exclusionary if the use does not meet the criteria for a moderate substance use disorder. Detailed information on inclusion and exclusion criteria is listed below (Textbox 2).

Participant inclusion and exclusion criteria.

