Eligibility measures and information collected during the preenrollment phone screen administered by authorized clinical researchers include The Ohio State University TBI Identification Method [92], the Columbia Suicide Severity Rating Scale [89], the UPPS-P [41], self-reported age, the ability to read and speak English, the Center for Magnetic Resonance Research safety form (Multimedia Appendix 2), and TMS safety form (Multimedia Appendix 4). If deemed eligible, participants will be asked to complete an in-person screening.

The in-person screening will consist of completing additional assessments to ensure eligibility and baseline characteristics. They include the structured diagnostic interview from the symptom attribution and classification algorithm, created by individuals involved in this study to determine likelihood and severity of prior TBIs [88], the Neurobehavioral Symptom Inventory, to determine TBI-related symptom presence [98], the Clinician-Administered PTSD Scale for DSM-5 to determine preexisting diagnosis of PTSD [99], the Alcohol Use Disorder Identification Test-Consumption Questions to determine if an alcohol use disorder is present [101], the Drug Use Disorders Identification Test to determine if a drug use disorder is present [102], and the Structured Clinical Interview for DSM-5–Research Version to determine the presence of other psychiatric disorders [104].

Once the listed diagnostic and screening measures are completed and participants meet eligibility criteria, participants will be asked to complete self-reported measures at their baseline, midpoint, and end point visits (Table 1).

Feasibility completion rates will be described according to the reasons participants did not complete the 2-week intervention and the rates of missed sessions. Study completion is defined as completing all 10 sessions. Safety measures will follow procedures used in prior TMS studies [125] and will be scored using the *Medical Dictionary for Regulatory Activities*. Side effects, AEs, and the TMS data safety sheet will assess change severity throughout the intervention. Tolerability will be measured through the number of patients who complete the treatment course and via self-report.

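### Pregnancy is an unqualified exclusion, but the only pregnancy test described is limited to sexually active women not on prescribed contraception

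*Protocol article*

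**What the plan says.** Textbox 2 of the protocol article lists pregnancy and breastfeeding among the exclusion criteria. The entry carries no condition about sexual activity or contraception.

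Study Procedures describes how pregnancy is tested. After consent, at the first in-person visit, a test is requested under this condition: "a woman, sexually active, and not on any form of physician-prescribed birth control, they will be asked to take a urine pregnancy test". No other pregnancy test appears in the article.

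The procedures that follow are fixed for everyone. The section on MRI acquisition and motor thresholding states: "All participants will undergo an MRI of their brain before and after iTBS administration". On finding the motor threshold it states: "Single pulse TMS will be administered to the left motor cortex at the hand knob". Study Procedures places the first MRI at visit 2 and motor thresholding at visit 3, with randomization and the ten treatment sessions afterwards.

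On the population, the Participants section states: "We will enroll 56 veterans aged between 22 and 65 years". It also says that nobody is excluded on grounds of sex or gender identity. The Recruitment section names a women's health clinic as one of the sources.

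**The concern.** The exclusion covers every pregnant candidate, while the test meant to enforce it covers only some of the women to whom it can apply. Both filters rest on facts that make pregnancy less likely without ruling it out. A contraceptive prescription does not show that the method is used correctly or that it works, and sexual activity is known only from what the candidate says.

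At stake is a pregnancy that the woman does not know about. If the written rule is followed exactly, such a woman in one of the two untested groups could be scanned and given single-pulse TMS although the protocol means to exclude her. Because those two visits precede randomization, this holds whichever arm she would later join. The point concerns participant safety and the enforcement of an eligibility criterion. It has no bearing on the sample size, the power or the mixed-model analysis of the SOFAS.

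**Working it through.** No arithmetic applies. The check sets the exclusion, the test rule and the visit sequence side by side.

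1. **Who must be excluded.** Any participant who is pregnant (Textbox 2).

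2. **Who is asked to take a test.** A participant who is a woman, and is sexually active, and is not on physician-prescribed birth control (Study Procedures). The three conditions are joined by *and*, so failing any one removes the request.

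3. **Who is left over.** Among women of childbearing potential, the rule sorts as follows:

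| Reports sexual activity | On physician-prescribed birth control | Test described |
|---|---|---|
| Yes | No | Yes |
| Yes | Yes | No |
| No | No | No |
| No | Yes | No |

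   One of the four combinations leads to a test. The rows are not equally common and the article does not say how women divide among them, so this is a description of the rule and not a proportion of women missed.

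4. **Whether the leftover group can exist in this trial.** Yes. Entry starts at age 22, women are eligible, and a women's health clinic is a recruitment source.

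5. **What comes next for them.** MRI at visit 2 and motor-threshold TMS at visit 3, both before randomization. No further pregnancy test is described before either.

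6. **Whether another described step closes the gap.** The MRI and TMS safety forms are administered by a rater at the phone screen (Table 1 and the text after it). Their content is in appendices that are not shown. If they ask about pregnancy, the answer is self-report, which cannot reveal an unrecognised pregnancy. The checks before and after each treatment session list vital signs, sleep, fatigue, recent seizures and tinnitus; pregnancy is not among them.

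7. **Whether this is only detail that a condensed article leaves out.** No. The article states who is asked and at which visit. The point is about the rule as written.

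**The case against.** The strongest reply is that nothing here is an error. An exclusion and a risk-based test can stand together, and the rule directs testing to the group most likely to be pregnant. Women reporting no sexual activity would add very little yield. Two institutional review boards reviewed and approved the protocol, which suggests a deliberate choice. Much of this stands: the two statements do not contradict each other, and the extra yield per woman is low. Approval does not show that the narrower rule is the better one, though, when the wider rule uses the same test at the same visit.

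A second reply is that other safeguards may exist out of sight. The safety forms are not shown, and scanning takes place at a separate imaging centre that may have its own pregnancy procedures. This also stands, and it limits what can be said. A reader might infer that women outside the rule actually reach the scanner and the coil untested. The article does not support that; it supports only that no test is described for them.

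Three further inferences should be resisted:

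- The electronic record review might be thought to act as a partial safeguard. Study Procedures describes it for demographics, diagnoses, medications, impulsive behaviour and implants, and does not mention pregnancy.
- Counting the scans and stimulation sessions that an untested woman would undergo might look like a measure of risk. Such a count describes procedures. It says nothing about how often the rule would fail or what harm would follow.
- The point might be read as a claim that MRI or TMS harms a fetus. The article contains no evidence on this, and none is needed: the argument rests on the sponsor's own decision to exclude pregnancy.

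**Conclusion.** The point holds in a limited form. The described test does not reach every woman to whom the pregnancy exclusion can apply: women of childbearing potential who are on prescribed contraception, or who report no sexual activity, have no described test before the first MRI and motor thresholding.

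The size cannot be stated as a number, because the article gives neither the expected number of women nor a pregnancy probability. The chance for any one woman is low. The conclusion rests on two assumptions: that the written rule is followed as it stands, and that no undescribed test at the imaging site fills the gap. If the imaging centre already tests every woman of childbearing potential before scanning, the practical gap before the visit 2 MRI closes, and the amendment would serve only to put that in the protocol. This is a cheap improvement in safety and eligibility checking, not a flaw that threatens the trial's validity.

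**What to change.** Amend the sentence in Study Procedures so that every woman of childbearing potential takes the urine pregnancy test at visit 1, before the first MRI, regardless of reported sexual activity or contraception. Define childbearing potential in the same place, so that staff apply the rule uniformly.

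The cost is at most one more urine test per woman screened in person, with a test and a visit already in the protocol, and slight participant burden. A minor amendment is also needed, with oversight by two review boards and enrolment under way. The Results section reports 2 of 56 participants enrolled as of July 2024, so up to 56 − 2 = 54 remained to be enrolled at that date; the number now remaining is not known from the article.

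The change is not a complete safeguard. A single test at visit 1 may miss a very early pregnancy and will not detect one that begins later in the study.
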